#### Statistical methods

Quantitative data will be analyzed using the statistical program SPSS 29.0 [69]. First, the items of the scales of the primary and secondary outcomes are checked for missing values. Items and complete sociodemographic variables that violate the MCAR (missing completely at random) assumption are identified in each subanalysis using Little’s MCARTest. Missing values are then estimated using the Markov Chain Monte Carlo (MCMC) procedure. This procedure yields reliable results even with high proportions of missing values for both the MCAR and MAR (missing at random) missing value patterns. On the other hand, it is suitable for any patterns of missing values, but also for monotonic patterns.

Descriptive analyses are calculated for all variables and presented as frequencies, means, standard deviations and ranges. Sociodemographic and medical predictors of intervention effectiveness are identified using stepwise backward regression. Non-dichotomous categorical characteristics are first subjected to multifactorial analysis of variance. Games-Howell correction or Bonferroni-Holm correction is used as a post hoc test, as appropriate. Correlation analysis is performed prior to each regression to avoid multicollinearity. Mean comparisons using one-way factor repeated measures analyses of covariance (ANCOVA) are used to test the hypotheses.

The first step is to compare only the randomized groups. In the next step, the preference groups are analyzed to determine differences in the effects compared to the randomization groups. Finally, all four groups are compared with each other, adding an indicator variable (randomization/preference) as a covariate. If the number of randomized study participants is too small, the data must be analyzed as a prospective cohort study.

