**Methods:**

A prospective Comprehensive Cohort Design with repeated measures will be used to evaluate the effectiveness of Peer2Me for AYA. A sample of 180 patients in active cancer treatment aged 18 to 39 years will be enrolled and randomized to the intervention or control condition (a single AYA-specific consultation). Following mentor training, mentees and mentors are matched by diagnosis, age, and gender. The primary outcome is self-efficacy; secondary outcomes include measures of anxiety, depression, health literacy, life satisfaction and social support life. Outcomes will be measured at baseline before the intervention (t1), immediately after completion of the three-month intervention (t2) and three months after completion the intervention (t3). For the final analyses, we will use an intention-to-treat approach (ITT) and compare patients in the assigned treatment groups.

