### Study design

The study is designed as a bi-center (university medical centers in Leipzig and Hamburg) comprehensive cohort study (CCD) [49] with a 1:1 allocation ratio over a period of 36 months and assessments at baseline and 3 and 6 months after the intervention. In this study design, eligible participants can choose to be randomized. In addition, patients who are not interested in participating in the Peer2Me intervention or the control group will be asked to complete the accompanying questionnaires at the three measurement time points. This will provide an additional no-intervention comparison group that will be relevant for comparison, in particular if the willingness to randomize in the study sample turns out to be very low.

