The intervention begins by matching the tandems (mentor and mentee) by age, diagnosis, and gender, if possible. At the first meeting of each tandem, a study staff member will be present to explain the Peer2Me study process and agenda, distribute cancer-specific and psychosocial information materials, and to conduct the baseline assessment (t1). Participants are either provided with a link to complete the standardized study questionnaire online using Lime Survey, or, if preferred, a printed version of the questionnaire is sent.

The tandem itself will then determine the frequency, duration, and type (face-to-face or telephone) of subsequent contacts between mentor and mentee over the following three months. However, at minimum of 4 documented contacts should take place for the purposes of the evaluation (fewer than 4 contacts are considered as a termination of intervention). The mentor documents each interaction, including the key issues discussed with the mentee, and informs the study team. After 3 months, a formal final meeting of the tandem will be held together with a member of the study team, during which the assessment t2 is conducted. The final survey (t3) will be sent to all mentees 3 months after the intervention.

Group supervision for the mentors will take place once a month. It will be provided by a psychologist with appropriate psycho-oncological and group therapy expertise.

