### Statistical analysis

#### Power and sample calculation

The number of cases was planned with the GPower program using a significance level of α = 0.05 and a power of (1-ß) = 0.8070. The primary outcome measure self-efficacy is used to demonstrate the effectiveness of the intervention. We make the following assumptions about changes in the intervention and control group: The pre-post effect size used is the effect size for self-efficacy.

d = 0.43, which could be found in the literature [68]. The expected controlled effect size requires a minimum of 90 subjects per group (180 subjects in total) measured with the U-test for independent groups. For this group size (*N* = 180), an analysis of variance with repeated measures (two groups, three measurements, correlation between measurements *r* = 0.5, epsilon = 1) can already demonstrate the following small effects: for comparisons between factors (IG vs. CG): f > 0.17; comparisons within factors (across measurement time points): f > 0. 09; and interaction effects between the two groups and time: f > 0.09. The sample thus has sufficient power to detect at least medium effects between the groups, as well as small effects within the groups and small interaction effects between the groups considering the measurement time points.

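### Imputation under MAR is called reliable even at high missingness, although a mentee's t2 score may be missing because mentoring stopped, so the assigned-group effect may be overstated

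*Protocol article*

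**What the plan says.** The Statistical methods section of the protocol article checks the scale items for missing values, applies Little's MCAR test, and then has missing values estimated by an MCMC procedure. The justification given is: "This procedure yields reliable results even with high proportions of missing values for both the MCAR and MAR (missing at random) missing value patterns". The next sentence calls the procedure suitable for any pattern, monotone ones included. The text therefore covers whole questionnaires lost after dropout as well as skipped items. Repeated-measures ANCOVA follows, first in the randomised groups only. The Methods part of the abstract labels the final analysis: "we will use an intention-to-treat approach (ITT) and compare patients in the assigned treatment groups".

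Data collection differs by arm. Under Intervention, mentees complete t2 at the formal closing meeting of the tandem with a study team member, and the t3 survey goes to every mentee. The same section says of the minimum number of contacts: "fewer than 4 contacts are considered as a termination of intervention". Under Control group, t2 and t3 are both requested by e-mail or mail, with reminders. The article gives no expected dropout rate.

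**The concern.** Reliability under MAR helps only if MAR is credible for the scores that will be missing. Here the plan's own procedure gives a reason for doubt. A tandem that ends early may never hold its closing meeting, and no other t2 route for mentees is described. A missing t2 can then be a direct result of stopping mentoring, in one arm only. Mentees are also in acute cancer treatment, so worsening illness is another plausible reason for not answering. Little's test, the only diagnostic named, cannot separate MAR from missing not at random.

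If the scores of mentees who stopped are predicted from mentees who completed, the estimate moves towards the effect had nobody stopped. The question under intention-to-treat is the effect of being assigned to Peer2Me, stoppers included. Part of a favourable result could then rest on imputed rather than observed benefit.

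**Working it through.** **The plan's own figure.** Under Power and sample calculation, the design "requires a minimum of 90 subjects per group (180 subjects in total) measured with the U-test for independent groups", with "significance level of α = 0.05 and a power of (1-ß) = 0.8070" and effect size 0.43. The normal approximation for a two-sided t-test at power 0.80 gives 2 × (1.960 + 0.842)² / 0.43² = 84.9, so 85 per group. Noncentral t gives 86. Allowing for the U-test's efficiency of 3/π = 0.955 gives 90, with power 0.8003 (92 would be needed for 0.807). The 90 reproduces, and this point does not touch it.

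**Inputs.** From the article: 90 per arm, d = 0.43, and "correlation between measurements *r* = 0.5, epsilon = 1". Assumed, because the article is silent: a share p of mentees stops (10%, 20% or 30%); completers gain 0.43; stoppers gain 0; and, to begin with, no stopper is observed.

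**True assigned-group effect.** 0.43 × (1 − p).

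**Arm in the imputation model, contact status not in it.** Stoppers are predicted from completers in their own arm: 0.43 × (1 − p) + 0.43 × p = 0.43.

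**Arm omitted, dropout in the intervention arm only.** Stoppers receive the pooled observed mean gain, 0.43 × (1 − p)/(2 − p). The estimate is 0.43 × (1 − p) × 2/(2 − p).

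**Arm omitted, equal dropout in both arms.** Every missing score, in either arm, receives the same pooled mean gain of 0.215, which cancels in the difference. The estimate is 0.43 × (1 − p).

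Simulated values are in brackets (90 per arm, correlation 0.5 with baseline, 10 imputations, 400 to 600 replicates, Monte Carlo standard error 0.005 to 0.008). In the third column the first is for dropout in the intervention arm only and the second for equal dropout.

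| p | True effect | Arm in model | Arm omitted, one-arm dropout | Arm omitted, equal dropout |
|---|---|---|---|---|
| 10% | 0.387 | 0.430 (0.421; 0.437) | 0.407 (0.401) | 0.387 (0.385) |
| 20% | 0.344 | 0.430 (0.419; 0.431) | 0.382 (0.383) | 0.344 (0.352) |
| 30% | 0.301 | 0.430 (0.429; 0.416) | 0.354 (0.349) | 0.301 (0.292) |

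With arm in the model the overstatement is 0.043, 0.086 or 0.129. In relative terms it is 1/(1 − p) − 1, that is 11%, 25% or 43%.

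**Some stoppers answer.** Let a share q of stoppers be observed. With arm but not contact status in the model, the estimate is 0.43 × (1 − p)/(1 − p + pq). At an illustrative q = 0.5 it is 0.387/0.95 = 0.407, 0.344/0.90 = 0.382 or 0.301/0.85 = 0.354, so the relative overstatement falls to 5%, 11% or 18%.

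**Contact status added.** Unobserved stoppers are now predicted from observed stoppers, whose gain is 0. The estimate is 0.43 × (1 − p) + 0 × p, the true value, provided that stoppers who answer resemble those who do not. If no stopper answers, the data cannot supply this term, and only a sensitivity analysis can show the dependence.

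**The case against.** The quoted sentence is confined to MCAR and MAR. Under true MAR with a sound model it is broadly right, and it claims nothing for data missing not at random. That stands: the fault lies in relying on MAR without support in this setting, not in a false statement about the method.

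Stopping mentoring is not leaving the study. The t3 survey goes to all mentees, so a stopper may be observed at t3 and is then not imputed for that visit. That also stands and reduces the bias.

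The size follows from the assumptions. Zero gain in stoppers is harsh after up to three contacts, and the article does not say what the imputation model contains. With arm omitted and equal dropout the bias vanishes. The figures therefore illustrate a range and do not measure a known error.

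A reader might go further and infer three things that the article does not support:

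- **A contradiction with intention-to-treat.** Imputing while keeping everyone in the assigned arm fits the abstract's definition.
- **Analysis of one completed data set without pooling.** The text does not say this.
- **No alternative analysis will be run.** Pooling rules, model terms and sensitivity analyses commonly sit in an analysis plan, and that document is not shown, so their absence here is no finding.

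What the objection leaves untouched is the difference in t2 collection between the arms, together with a reliability statement that takes no account of it.

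**Conclusion.** The point holds as a conditional one. The plan relies on MAR for dropout and presents this as reliable at high missingness, while its t2 procedure makes missingness that depends on stopping plausible in the intervention arm. If stoppers are unobserved, gain less than completers, and the model contains arm but not contact status, the assigned-group effect may be overstated. In the extreme case of zero gain and no observed stoppers, about 0.43 would be reported against 0.39, 0.34 or 0.30 at an assumed 10%, 20% or 30% missing. Answers from stoppers reduce this, and under the same assumptions omitting arm with equal dropout removes it.

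It would be too strong to say that early leavers are credited with the completers' benefit, because the article does not fix the conditions for that. The rating is a cheap improvement.

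**What to change.** 1. Reword the reliability sentence so that it applies only where MAR holds, and say that MAR is doubtful for mentees who ended mentoring.
2. State that the imputation model contains arm, earlier scores and the documented number of contacts (or termination status). Mentors already record each contact. Contacts occur after randomisation, so they belong in the imputation model only and not among the ANCOVA covariates.
3. Name one sensitivity analysis of the randomised comparison in which terminated mentees without later data are imputed from the control group, or with a delta stated in advance. Report it beside the main result.

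If the analysis plan already contains items 2 and 3, confirming this and making item 1 is enough. No new data are needed. The cost is some wording, a few extra runs and possibly a less favourable sensitivity estimate.

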#### Posttraumatic growth inventory (PTGI)

The Posttraumatic Growth Inventory (PTGI) measures the extent to which patients have experienced positive changes regarding cancer [67]. The questionnaire contains 21 items in five domains: new opportunities, relationship with others, personal strength, appreciation of life, and spiritual change. Using a five-point Likert scale, patients indicate the extent to which the item statements apply. Item scores are summed to a total score, with higher scores indicating higher posttraumatic growth. The PTGI is a reliable and valid instrument that has been translated into several languages.

**Table 1 Tab1:** Study instruments

	Screening t0		Baseline t1		follow-up t2		follow-up t3	
instrument	mentor	IG/CG	mentor	IG/CG	mentor	IG/CG	mentor	IG/CG
sociodemographic	X	X						X
clinical variables	X	X						X
psychosocial variables	X	X			X	X		X
SCID-5-CV	X							
GSE				X		X		X
PTGI			X		X			
SPF			X		X			
CBI-B				X		X		X
GAD-7				X		X		X
PHQ-9				X		X		X
BSSS				X		X		X
FLZ-M			X	X	X	X		X
HLS-EU-Q16				X		X		X

Notes. IG = intervention group (mentees), CG = control group, SCID-5-CV = Structured Clinical Interview for DSM-5 Disorders Clinician Version, GSE = General Self-Efficacy Scale, PTGI = Posttraumatic Growth Inventory, SPF = Saarbrücken Personality Questionnaire on Empathy, CBI-B = Cancer Behavior Inventory - Brief Version, GAD-7 = Generalized Anxiety Scale, PHQ-9 = Patient Health Questionnaire Depression Module, BSSS = Berlin Social Support Scales, FLZ-M = Questionnaire of life satisfaction, HLS-EU-Q16 = European Health Literacy Survey Questionnaire

As part of the study, sociodemographic data, including age, partnership status, number of children, and employment status, were collected from all participants at t1. Additionally, clinical variables—such as diagnosis, time of diagnosis, and therapies—were recorded through self-report. Psychosocial variables encompassed the utilization of psychosocial support services and general inquiries into mental health, all of which were also documented at t1.

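### Predictors of the Peer2Me effect are sought by backward stepwise regression, which as described does not target effect modification and has no stated control of selection error

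*Protocol article*

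**What the plan says.** The protocol article gives this analysis one sentence under Statistical methods: "Sociodemographic and medical predictors of intervention effectiveness are identified using stepwise backward regression". Two preparatory steps surround it. For variables with more than two categories: "Non-dichotomous categorical characteristics are first subjected to multifactorial analysis of variance". For collinearity: "Correlation analysis is performed prior to each regression to avoid multicollinearity".

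Multiplicity is mentioned only for post hoc comparisons: "Games-Howell correction or Bonferroni-Holm correction is used as a post hoc test, as appropriate". The hypotheses have a separate analysis: "Mean comparisons using one-way factor repeated measures analyses of covariance (ANCOVA) are used to test the hypotheses".

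For the stepwise regression, the article names no outcome, candidate list, retention threshold, analysis set or arm-by-covariate term, and it does not label the analysis exploratory. None of Hypotheses I-IV under Aim concerns predictors of the effect.

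**The concern.** A predictor of effectiveness is a variable across whose levels the difference between arms changes. In a regression, the arm-by-covariate interaction estimates that. Backward elimination on main effects answers another question, namely which variables go with a higher or lower outcome. A variable that predicts self-efficacy equally well in both arms says nothing about who benefits from Peer2Me, yet such a model would tend to keep it.

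Stepwise elimination also tests many variables and reports the survivors. The p-values of the survivors take no account of that search, and the article states no correction for it.

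At stake is a supplementary statement about who gains from the programme. It could be published as a finding although it reflects prognosis or chance.

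**Working it through.** **Inputs from the article**
- Sample size: 90 per group, 180 in total, planned "using a significance level of α = 0.05 and a power of (1-ß) = 0.8070", with d = 0.43 and a U-test (Power and sample calculation).
- Candidates (text below Table 1): "sociodemographic data, including age, partnership status, number of children, and employment status, were collected from all participants at t1", plus clinical variables "such as diagnosis, time of diagnosis, and therapies". That is at least 4 + 3 = 7, and both lists are open-ended.

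**Assumptions not in the article**
- 7 or 10 independent candidates.
- Retention threshold 0.05 or 0.10.
- In step 2, one prognostic variable with r = 0.3 and no effect modifier.

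**The plan's own figure.** Two-sided, n per group = 2(1.96 + 0.842)²/0.43² = 84.9, rounded up to 85. Multiplying by π/3 for the U-test gives 89.0. The t-based version gives 85.9 × π/3 = 89.9, so 90. Power at 90 per group is 0.800 to 0.805. The planned size reproduces, and N = 180 is used below.

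**Step 1: chance selection when nothing predicts.** P(at least one kept) = 1 − (1 − threshold)^k. Each simulation here and below used 1,000 trials per setting. The simulated range covers three models: main effects in the intervention arm, main effects in both arms, and interaction terms.

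| Candidates k | Threshold | Formula | Simulated |
|---|---|---|---|
| 7 | 0.05 | 1 − 0.95^7 = 30% | 29-33% |
| 7 | 0.10 | 1 − 0.90^7 = 52% | 53-56% |
| 10 | 0.05 | 1 − 0.95^10 = 40% | 42-43% |
| 10 | 0.10 | 1 − 0.90^10 = 65% | 65-66% |

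The rate hardly depends on the model, so this part of the point holds whether or not interactions are fitted.

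**Step 2: one purely prognostic variable, no modifier.** Share of trials in which that variable is kept:

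| Candidates, threshold | Main effects, intervention arm | Main effects, both arms | Interaction terms |
|---|---|---|---|
| 7, 0.05 | 81% | 98% | 5% |
| 7, 0.10 | 90% | 99% | 10% |
| 10, 0.05 | 84% | 98% | 5% |
| 10, 0.10 | 89% | 99% | 13% |

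Hand check: the expected test statistic is about 0.3 × √n / √(1 − 0.3²). For n = 90 it is 2.98, so the chance of passing 1.96 is Φ(1.02) = 85%. For n = 180 it is 4.22, giving Φ(2.26) = 99%. Both are close to the simulation. With interaction terms the rate stays near the nominal threshold.

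**Step 3: one true modifier present.** The assumed interaction is 0.43 SD per SD of the covariate, with equal and opposite slopes in the two arms. Runs had either no prognostic covariate or two.

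| Model | True modifier found | Share of selected variables that are not modifiers |
|---|---|---|
| Main effects, both arms | 5-12% | 85-97% |
| Main effects, intervention arm | 49-66% | 38-59% without prognostic covariates, 77-80% with two |
| Interaction terms | 77-87% | 27-54% |

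The opposite slopes cancel on average. That is why the main-effects model in both arms finds the modifier at little more than the chance rate.

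**Step 4: power of an interaction test.** Take two equal subgroups, so 45 patients per arm-by-subgroup cell. SE = √(4/45) = 0.298 SD. For an interaction of 0.43 SD, 0.43/0.298 = 1.44, and power = Φ(1.44 − 1.96) = 30%. This effect is half as large as in step 3: a half/half indicator has SD 0.5, so 0.43 between halves is 0.215 per SD.

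**The case against.** The strongest objection is that the missing interaction term is inferred from silence. The article condenses a fuller plan that is not shown, and backward elimination over arm-by-covariate terms would fit its sentence. This stands in part. Main effects are the more natural reading, because the power section names group-by-time interactions where they are meant and no arm-by-covariate term appears anywhere. It remains a reading, not a statement in the text. The lack of stated selection control does not depend on it, because step 1 gives the same rates with interaction terms.

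A reader might infer that most predictors reported by this trial would be false. The documents do not support that. The false share depends on a model the article does not specify. It is 85-97% for main effects in both arms, 38-80% in the intervention arm alone, and 27-54% with interaction terms. With 7 null candidates at 0.05, about 70% of trials would report no predictor at all.

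A reader might also infer that candidates are screened against the outcome by correlation. The text gives collinearity as the purpose of that step, so it is no part of the problem.

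Finally, the analysis is supplementary, and the article mentions no plan to choose patients by predictor. Both points are correct and limit the weight of this comment.

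**Conclusion.** The point holds as a modest, inexpensive improvement to a supplementary analysis. Backward stepwise regression is a stated choice, so this is more than missing detail. On the main-effects reading it would present prognostic variables as predictors of effectiveness in most trials that contain one: 81-99% retention, against 5-13% with interaction terms. On any reading it would keep at least one chance predictor in about 30-65% of trials where nothing predicts.

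These figures rest on the assumed candidate number, independence, thresholds and r = 0.3. The direction of the result does not depend on the exact values. It would be wrong to conclude that the trial's main result is at risk, since the tests of Hypotheses I-IV do not use this regression.

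**What to change.** Replace the stepwise sentence with wording such as: *Effect modification will be examined in the randomised set by adding arm-by-covariate interactions, one at a time, to the primary model for a short pre-specified list (for example age, gender, diagnosis group and baseline self-efficacy). Interaction estimates will be reported with 95% confidence intervals, adjusted for multiplicity by Holm's method and labelled exploratory.*

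Add a provision for the planned fallback: if too few patients accept randomisation and the data are analysed as a cohort, fit the same interaction models with the randomisation/preference indicator and label the results non-randomised. The collinearity check may stay.

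The change needs no new data. Age and gender are stratification factors, diagnosis is recorded, and self-efficacy is measured at t1. The cost is low power, about 30% before adjustment (step 4). With four variables, the strictest Holm step uses 0.05/4 = 0.0125 (critical value 2.50), and power falls to Φ(1.44 − 2.50), about 15%. Few modifiers will be declared, so the estimates and their intervals should carry the message.

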### Randomization

The Comprehensive Cohort Design (CCD), or Patient Preference Trial, is an alternative to a randomized controlled trial. It is used when patient preference needs to be taken into account or when it is hypothesized that there is a relatively high preference for participation in a particular intervention [49, 54]. In the CCD, potential study participants are asked at the start of the trial if they agree to be randomized. If they agree, randomization takes place. If they refuse randomization, they can choose which study arm they will be assigned to. The CCD offers several advantages that are crucial for the successful implementation of this psycho-oncological intervention study, such as the possibility to include all potential study participants (including patients who refuse randomization) and a lower drop-out-rate in the control arm. If randomization is sufficient, an analysis similar to the RCT study is possible.

A limitation of the CCD is the difficulty in predicting the willingness of participants to be randomized. It is not possible to make clear statements about this in advance, especially as the present mentoring project is the first peer-supported intervention for young adult cancer patients in Germany.

If a sufficient number of study participants have been randomized in each study arm, analyses will be performed within the randomized arms and the non-randomized participants will be used to check external validity. If insufficient participants agree to randomization, all data will be analyzed as a prospective cohort study.

Potential study participants are fully informed about the study, the different study arms, and the main data to be collected. As a next step is to check the inclusion criteria and determine whether randomization can take place or whether there is a clear patient preference.

Randomization of study participants is performed within three working days by an independent documentation assistant of the Leipzig study center using the randomization software RITA. Block randomization with variable block length will be used to achieve a better balance. Stratification by gender and age will be performed for each study center to ensure structural equality for the intervention and control groups.

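### The hypothesis test does not fix the covariates, the repeated levels or the deciding term; a t1-adjusted contrast at t2 would have about 91% power, against about 85% for the interaction and 65% for the group main effect

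*Protocol article*

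**What the plan says.** Three places in the protocol article bear on this.

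- **Statistical methods** gives the test: "Mean comparisons using one-way factor repeated measures analyses of covariance (ANCOVA) are used to test the hypotheses". The randomised groups are compared first, then the preference groups, then all four groups together. The only covariate named is the randomisation/preference indicator, and it enters at the four-group step.
- **Power and sample calculation** sizes the trial with a U-test at "significance level of α = 0.05" and "a power of (1-ß) = 0.8070", which leads to 90 per group. The effect is "d = 0.43, which could be found in the literature [68"], introduced by the sentence "The pre-post effect size used is the effect size for self-efficacy" and then used as the controlled effect. The section goes on to give detectable effects for "an analysis of variance with repeated measures (two groups, three measurements, correlation between measurements" r = 0.5, epsilon = 1): "for comparisons between factors (IG vs. CG): f > 0.17" and f > 0.09 for both the time effect and the group-by-time interaction.
- **Randomization** states: "Stratification by gender and age will be performed for each study center".

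The Primary outcome section places the between-group comparison at t2 and t3. The Aim section words Hypothesis I as a greater increase in self-efficacy than in the control group, lasting at least three months.

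**The concern.** Self-efficacy is measured at t1, t2 and t3 (Table 1), so a model with three measurements includes t1 as an outcome. Randomisation makes the expected group difference at t1 zero. A group main effect over three waves therefore averages one null time point with two that may carry the effect. The group-by-time interaction avoids this dilution, but it is a 2-df omnibus test. It does not by itself show a benefit at t2 or its persistence at t3, which are what the hypotheses claim.

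The methods sentence does not settle which of these is meant. The phrase one-way factor fits poorly with the two-factor model of the power section, and the covariate in the randomised comparison is not identified. Two things are at stake: power that the t1 score could supply from data already being collected, and a deciding term that could be chosen after the results are seen. If the stratification factors predict self-efficacy, leaving them out of the model also makes the standard errors larger than they need to be.

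**Working it through.** **Inputs from the plan:** 90 per arm (N = 180), alpha 0.05 taken as two-sided, m = 3 measurements, r = 0.5, epsilon = 1, d = 0.43. **Assumptions added here:** d is a between-group difference in SD units; the difference is 0 at t1 and 0.43 at both t2 and t3; SDs are equal across waves; all 90 per arm are analysed.

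**1. The plan's own figures.** The two-sided U-test (noncentral t with n multiplied by 3/π) gives 90 per group at 80% power, as stated. For the repeated-measures ANOVA:
- Between groups: λ = f²·N·m/(1 + (m − 1)r) = f²·540/2 = 270f². 80% power is reached at f = 0.171 (stated 0.17).
- Time and interaction: λ = f²·N·m/(1 − r) = f²·540/0.5 = 1080f². 80% power is reached at f = 0.095 (stated 0.09).

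Both statements reproduce.

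**2. Group main effect over three waves.** Mean difference = (0 + 0.43 + 0.43)/3 = 0.287, so f = 0.287/2 = 0.143. λ = 270 × 0.143² = 5.55 on (1, 178) df. Power = **64.9%**.

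**3. Group-by-time interaction.** The squared deviations of (0, 0.43, 0.43) from 0.287 sum to 0.1233. f = √(0.1233/12) = 0.101 and λ = 1080 × 0.101² = 11.09 on (2, 356) df. Power = **85.3%**.

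**4. t1-adjusted contrast at t2.** Residual variance = 1 − 0.5² = 0.75. SE = √(0.75 × 2/90) = 0.129. λ = (0.43/0.129)² = 11.09 on (1, 177) df. Power = **91.2%**. The noncentrality equals that of the interaction; the gain comes from spending one df instead of two.

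**5. t1-adjusted mean of t2 and t3.** Residual variance = (1 + 0.5)/2 − 0.25 = 0.5. λ = 0.43²/(0.5 × 2/90) = 16.64. Power = **98.2%**, but only if the effect does not fade.

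**6. Sensitivity.**

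| Scenario | Group main effect | Interaction | t1-adjusted t2 |
|---|---|---|---|
| Flat effect, r = 0.5 | 64.9% | 85.3% | 91.2% |
| Fades to 0.20 at t3, r = 0.5 | 40.4% | 73.2% | 91.2% |
| Flat effect, r = 0.3 | 74.5% | 70.9% | 85.3% |
| Flat effect, r = 0.8 | 53.8% | 99.8% | 99.8% |

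The advantage over the interaction is about 6 points at the planned r. It is about 14 points at r = 0.3 and 18 points if the effect fades to 0.20, and it vanishes at r = 0.8.

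**The case against.** The strongest reply is that nothing in the article says t1 is a level instead of a covariate in the hypothesis test. Three measurements appear only in a supplementary sensitivity calculation. The test itself is called an ANCOVA, and its covariate in the randomised step cannot be the randomisation/preference indicator, which is constant there. It could be t1, and the t2 and t3 comparison in the Primary outcome section fits that reading. This stands: a reader might infer that the plan discards the baseline, but the documents leave it open.

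Second, a reader might set 65% against 91% or 98% as the loss. That requires the group main effect to decide. The power section explicitly lists the interaction, which suits a hypothesis about differential increase and exceeds the planned 80% under the flat profile. One-way may also mean a single between-subject factor, so it does not prove that the interaction is absent. This stands too, and it reduces the gain to about 6 points.

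Third, a reader might call the f > 0.17 statement false, because d = 0.43 averages to f = 0.143 over three waves. The statement is only a minimum detectable effect. It reproduces, and the plan never says that its d meets it for that term.

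Fourth, a reader might expect patients with a missing wave to be dropped. The Statistical methods section imputes missing values by MCMC, which answers this.

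Finally, an article may leave a full covariate list to an SAP. That is fair, and the omission of the strata is not an error in itself. What remains is that the test as described names no covariate for the randomised comparison and no deciding term, and that its wording does not match the power section.

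**Conclusion.** The point holds as a free improvement, not as an error in a stated figure. The model behind the sensitivity figures counts t1 as an outcome, the named test is worded differently, and the article fixes neither the covariates nor the deciding term for the randomised comparison. On the plan's inputs that choice moves power from about 65% (main effect) through 85% (interaction) to 91% (t1-adjusted at t2). Against the most natural reading of the current text, the interaction, the gain is about 6 points. It is larger if the effect fades or r is below 0.5, and smaller if r is higher.

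The sizes rest on the flat effect profile, on reading d = 0.43 as a between-group difference although it is introduced as pre-post, and on 90 analysed per arm. The gain from the stratification factors cannot be quantified from the article. The adjustment also needs a t1 unaffected by allocation: the Intervention and Control group sections place the t1 survey at the first tandem meeting and at the control consultation, when the arm is already known.

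**What to change.** State the analysis of the randomised groups as follows:

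- Outcomes: the scores at t2 and t3.
- Fixed effects: arm, time, arm × time, t1 score, centre, gender and age.
- Model: a linear mixed model, or ANCOVA at each wave on the imputed data. Either serves.
- Primary contrast: IG minus CG at t2. The t3 contrast from the same analysis addresses persistence.
- Sensitivity figures: replace those for the three-measurement ANOVA with figures for this model, stating the assumed effect at t2 and t3.
- Timing: have t1 completed before allocation is known. Where that was not done, say so and treat the t1 adjustment with corresponding caution.

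The analysis change costs only wording in the plan. It needs no extra patients or assessments, and SPSS, the software already named, fits such models. The timing of t1 is the one operational element, and it can change only for patients not yet enrolled.
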